#### Population and sampling

30 General practices from the Amsterdam (*n* = 15) and Nijmegen (*n =* 15) areas (Fig. 2) will be included. Practices will be included purposefully to comprise a broad spectrum of practice characteristics based on level of urbanisation, practice size and social-economic status of the practice area. [name] and [name] observed that group practices tend to be more at risk for discontinuity (unpublished results, see Additional file 2). Therefore, only general practices employing three or more GPs will be included.

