**Table 1 Tab1:**
[figure not shown]
Schedule of enrollment, intervention and follow-up

The secondary outcome measurements during the trial will constitute the process evaluation. This will include measuring implementation, acceptability and feasibility of the TOOL-kit and performing an analysis of barriers and facilitators for successful implementation (Table 1).

Implementation will be evaluated using the guidance proposed by Saunders et al. [67]: the extent to which the components of the TOOL-kit are performed as planned (fidelity), the degree to which the components were provided to GPs and practice assistants (dose delivered) and the extent to which these participants have adopted the components in daily practice and are performing the desired behaviour (dose received).

The acceptability and feasibility of the TOOL-kit will be determined by evaluating the experiences of the GPs and practice assistants with the intervention. This will include the satisfaction with the intervention, its perceived appropriateness to daily practice, work related stress, job satisfaction and support among participants for continued use of the TOOL-kit.

Barriers and facilitators as experienced by the GPs and practice assistants will be collected using a framework proposed by Fleuren et al. (see Additional file 3) [68]. This framework includes 50 factors that can influence the implementation difficulty of a health care innovation.

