#### Sample size

The sample size calculation was based on our primary outcome measure (the NCQ). For both NCQ distribution cycles in month 0 and month 12, we will approach 100 patients per practice. We expect at least 35 patients per practice to participate, resulting in a total of 1050 patients in each cycle. When the mean NCQ score is compared between cycles using a mixed linear model with a random effect for practice and two-sided testing at a significance level of 5%, the expected sample size allows detection of all standardized effect sizes of 0.12 and larger with at least 80% power irrespective of the intra-cluster correlation coefficient. The standardized effect size is defined as the difference in means divided by the total standard deviation incorporating both the between- and within-practice variation.

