### Phase IV: implementation

During the final phase, the conditions for large-scale implementation will be defined using the results from phase III. Barriers and facilitators to implementation and potential adverse effects will be determined. For further implementation, local stakeholders and national GP organisations will be involved to integrate the use of the TOOL-kit in daily general practice.

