#### Trial (phase III)

Descriptive statistics will be used to summarize population characteristics. For the primary analysis, the mean NCQ score at baseline and at 12 months follow-up will be compared using a linear mixed model with a random effect for practice and a fixed effect for time point. To analyse if differences depend on longer exposure to the TOOL-kit, the main effect of wedge number and the two-way interaction between wedge number and time point will be determined.

Secondary outcomes measures from the surveys will be compared before and after the intervention and between measurements on different time points using mixed linear models or generalized estimating equations depending on the type of outcome measure. This accounts for clustering of participants within the practices. For outcomes that are collected in more than two periods, the length of exposure to the TOOL-kit main determinant will be considered using the control condition as a reference. A two-sided significance level of 5% will be used for all analyses.

The semi-structured telephone interviews will be analysed according to the framework method described in the *focus groups* section.

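### With only 30 practices, standard GEE inference does not deliver the stated 5% level for tests of exposure length on non-continuous staff outcomes; the plan should name a small-sample method

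*Protocol article*

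**What the plan says.** The phase III analysis section of the protocol article makes three choices for the staff survey outcomes.

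- Model: "using mixed linear models or generalized estimating equations depending on the type of outcome measure". Read plainly, continuous outcomes go to linear mixed models and other types to GEE. The stated reason is clustering within practices.
- Determinant: "For outcomes that are collected in more than two periods, the length of exposure to the TOOL-kit main determinant will be considered", with the control condition as reference.
- Level: "A two-sided significance level of 5% will be used for all analyses".

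The number of clusters is set under Population and sampling ("30 General practices from the Amsterdam" and Nijmegen areas), with at least three GPs and one practice assistant in each. Randomisation and blinding gives three wedges, starting at month 0, 3 or 6. Data collection gives staff surveys at months 0, 3, 6, 9, 12, 15 and 18.

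The article names no variance estimator, reference distribution or coding of exposure length for GEE.

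**The concern.** The usual GEE standard error is the robust (sandwich) estimator, judged against normal or chi-square critical values. Both are large-sample devices, and the sample size that counts is the number of clusters, here 30. With few clusters the sandwich variance is biased downwards and is itself noisy, and normal or chi-square values ignore that noise. The error grows with the number of parameters tested together, and the exposure factor can have up to six levels.

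An analyst who follows the article with software defaults would therefore report exposure-length p-values that are too small and confidence intervals that are too narrow, while the paper states a 5% level. At stake is the reading of whether staff outcomes change with longer use of the TOOL-kit.

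**Working it through.** **1. The plan's own figure.** The only computed figure is in the Sample size section and concerns the primary outcome: a standardized effect of 0.12 with "at least 80% power irrespective of the intra-cluster correlation coefficient". With 1050 patients per cycle, SE = √(2/1050) = 0.0436, and the detectable effect at ICC 0 is (1.960 + 0.842) × 0.0436 = 0.122. Power at 0.12 is Φ(0.12/[0.0436 × √(1 − ICC)] − 1.960): 78.5% at ICC 0, 80.5% at 0.05, 82.6% at 0.10. The figure is reproduced within 2 points. It involves no GEE and is untouched by this point.

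**2. Exposure levels (from the rollout and survey months).**

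- Wedge 1: 3, 6, 9, 12, 15, 18 months
- Wedge 2: 3 to 15 months
- Wedge 3: 3 to 12 months

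So there are six non-zero levels. Only wedge 1 reaches 18 months, which is 10 practices if the wedges are equal (assumed; the article gives no split).

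**3. Effect of the reference distribution alone.** Suppose the Wald statistic divided by its q degrees of freedom followed F(q, 30 − p), with p the number of regression parameters, but was judged against chi-square. The rejection rate would be P(F > χ²₀.₉₅,q / q).

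| q | χ²₀.₉₅/q | No period terms | With six period terms |
|---|---|---|---|
| 1 | 3.84 | df 28: 6.0% | df 22: 6.3% |
| 3 | 2.60 | df 26: 7.3% | df 20: 8.0% |
| 6 | 2.10 | df 23: 9.3% | df 17: 10.7% |

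This is a guide only. The downward bias of the sandwich adds to it.

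**4. Simulations under no effect.** All use 30 practices, 10 per wedge, four respondents per practice and seven waves. Period terms are shown both ways because the article does not say whether they are included.

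*Simulation A*: 1,300 trials, binary outcome near 60%, 75% response per wave, logit-scale variances 0.10 (practice), 0.10 (practice by wave) and 0.8 (person), exchangeable working correlation.

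| Test | Uncorrected, no period / period | Mancl-DeRouen with F or t |
|---|---|---|
| Joint, six levels | 15.7% / 18.3% | 6.4–6.5% |
| Single exposure contrasts | 4.6–6.8% / 5.9–7.7% | 3.6–5.0% |
| Before/after | 5.0% | – |

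Monte Carlo SE is √(0.157 × 0.843/1300) = 1.0 point for the joint test and √(0.05 × 0.95/1300) = 0.6 point near 5%.

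*Simulation B*: 2,000 trials per setting, full response, variance shares 0.10 (practice), 0.30 (person) and 0.05 (practice by period), independence working correlation, exposure coded linearly, in three categories (3, 6, 9 or more months) or on/off.

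| Test | Binary outcome, no period / period | Continuous outcome, no period / period | Corrected with F, all four |
|---|---|---|---|
| Linear, 1 df | 5.9% / 7.4% | 6.8% / 8.4% | 4.2–4.6% |
| Three categories, 3 df | 9.2% / 10.4% | 9.3% / 12.2% | 4.5–5.4% |
| On/off, 1 df | 6.8% / 6.9% | 7.0% / 7.7% | 3.9–4.5% |

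The binary columns are the relevant ones, since the plan appears to use linear mixed models for continuous outcomes.

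*Repeats of the six-level test* gave 16–20% uncorrected. With the corrected variance and F/t reference, results ranged from 2.4–4.1% in one repeat to about 5%, and up to 9% in one setting, in another.

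**5. Reading.** The simulations agree on the pattern: slight inflation at 1 df, about double at 3 df, three to four times nominal at 6 df. They differ a little on the plain before/after or on/off contrast (5.0% in A, 6.8–7.7% in B), so that contrast is at most slightly inflated.

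**The case against.** The strongest reply is that the article does not commit to an uncorrected sandwich variance, a chi-square reference or a six-level joint test. GEE is one of two model classes, it is unknown which outcomes would need it, and a journal article commonly leaves estimator details to the full protocol or analysis plan, which is not shown. A routine correction compatible with the text brings the tests close to 5%. This stands as a limit on the claim: the failure is conditional on standard inference, and the 16–20% applies only to the joint six-level test. It does not remove the point, because the article itself fixes the method, the determinant, the number of clusters and the level, and the usual form of that combination misses the level.

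Three stronger readings are tempting and are not supported.

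- **Multiplicity.** A reader might infer that many comparisons over outcomes and waves break the 5% promise. The statement sets a level per test and claims no familywise control. These outcomes are labelled a process evaluation, and the number of tests is not given. "This framework includes 50 factors that can influence the implementation difficulty of a health care innovation" describes how barriers and facilitators are collected, not a programme of 50 tests at every pair of waves. The baseline survey also covers only barriers and facilitators.
- **Phase IV.** A reader might infer that implementation conditions will rest on false positives. The article says "Barriers and facilitators to implementation and potential adverse effects will be determined", drawing on phase III results, which include telephone and group interviews. Nothing ties these decisions to p-values.
- **Missing data.** GEE needs stronger missingness assumptions than a mixed model, and the Discussion expects pandemic effects. But the article states no missingness mechanism and announces extra reminders, and Simulation A used a flat 75% response, so bias from selective non-response was not tested.

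**Conclusion.** The point holds in a limited form and is minor. If non-continuous staff outcomes are analysed by GEE clustered on 30 practices with standard inference, the 5% level is not delivered for the exposure-length tests. The size depends on the coding of exposure: about 5–8% for single or linear terms, 9–12% for a three-category term and 16–20% for a joint six-level test. The before/after contrast is not materially affected, and the primary NCQ comparison is not affected.

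The rates rest on assumptions that the article does not supply: 10 practices per wedge, four respondents per practice (the stated minimum), the variance components, the response rate and the prevalence. The ordering of the tests does not hinge on one set of these, since different variances, working correlations and response rates gave the same pattern.

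**What to change.** Add one sentence to the phase III analysis section: non-continuous survey outcomes will be analysed by generalized linear mixed models, or by GEE with a small-sample-corrected variance (Mancl-DeRouen or Kauermann-Carroll) and t or F reference values with between-practice degrees of freedom. It would help to state the coding of exposure length in the same place, because the inflation depends on it.

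Of these options, only the Mancl-DeRouen type with F/t reference was simulated here. It came close to 5% in most settings but not all (2.4% to 9%), so it is an improvement and not an exact guarantee.

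The cost is somewhat wider intervals and some loss of power on the process outcomes. No change to recruitment, data collection or the primary analysis is needed.

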## Discussion

This protocol paper describes a multi-phased approach to develop and evaluate a complex intervention for optimising personal continuity for older patients in general practice. Older patients receiving a higher level of continuity of care are likely to be more satisfied and experience a better relationship with their GP [11, 15–17, 23, 53], have a stronger sense of responsibility of their GP [56], a better quality of life [13, 19, 21], less overuse of medical procedures [22], and fewer hospital admissions [11, 23–26]. GPs providing a higher level of personal continuity are more satisfied with their job and perceive to have a better relationship with their patients [15, 16, 18]. In addition, personal continuity improves the uptake of preventive care by patients [11, 14], and increases medication adherence [13].

This study uses the MRC framework to develop and evaluate a complex intervention. The MRC framework was specifically designed to address problems that may arise during the development en evaluation of complex interventions, such as identifying the active ingredient of the intervention and transferability of results [49]. By using the MRC framework, we aim to address these challenges and increase reproducibility of intervention and results.

To our knowledge, this study is the first to investigate an intervention for improving personal continuity in general practice. Therefore, the results of our study will fill an important, previously described, gap of knowledge in respect to interventions for improving personal continuity in general practice [36, 70]. Another strength is the pragmatic nature of the study which enables evaluation of the TOOL-kit as if it would be applied in real-life general practice. This could improve the applicability and external validity of results [71, 72] and may facilitate future implementation [72].

Phase III and IV of the study will probably take place during the current SARS-CoV-2 (coronavirus) pandemic. Because especially complex interventions interact with the context they are performed in, [73] it is likely that the effect of the intervention will be affected by the coronavirus pandemic. We aim to mitigate this effect by dedicating part of the interviews and surveys in our process evaluation to the influence of the coronavirus on general practice. Additional reminders will be sent to reduce non-response and practices will be contacted periodically to assess trial feasibility within that practice and to tailor design adaptions when necessary and where possible.

All phases of the study will focus on personal continuity in Dutch general practice. Although this increases the relevance of the study results for Dutch clinical practice and healthcare policies, additional translational steps may be required to ensure its relevance in other countries.

In summary, the overall aim of this study is to develop and evaluate a complex intervention for improving personal continuity: the TOOL-kit. We will do this by performing a literature study (phase 0), a survey, focus groups and a Delphi study (phase I) followed by a pilot (phase II) and a cluster randomised stepped wedge pragmatic trial (phase III). We will use the results of phase III to define the conditions for further implementation of the TOOL-kit (phase IV).

## Data Availability

The dataset(s) supporting the conclusions of this article will be made available in the DataverseNL UBVU after data collection has ended. The details of intended methods of data entry, coding processes and measures to promote data quality and security are described elsewhere (see Additional file 4).

## Abbreviations

EMR: Electronic Medical Record
GP: General practitioner
MRC: Medical Research Council
NCQ: Nijmegen Continuity Questionnaire
NHG: Dutch College of GPs
RCGP: Royal College of General Practitioners
